**Data analysis**

The primary analysis of the difference in attack rate by study arm will be based on the overall meningitis incidence during the epidemic in villages of each arm after inclusion in the study, taking into account the cluster-randomized nature of the trial. Pairwise comparisons will be made between each intervention group using the student’s t-test. ANOVA and multiple linear regression will be used to compare the attack rates between the three study groups, and will be expressed in hazard ratios with 95% confidence intervals. The sponsor will be responsible for developing a written analytic plan.

The analysis of the resistance sub-study will be done on the basis of the per-protocol population for whom all three stool samples are available. Acquisition rates at 7 and 28 days following the initial sample will be calculated with corresponding 95% confidence intervals using the binomial distribution. The random selection of participants and households nested into a cluster-randomized design will be taken into account.

All P values will be 2-sided with *p* < 0.05 considered statistically significant. All other analyses of secondary analyses would be best regarded as exploratory, and any significant findings for these endpoints would need to be confirmed with further studies. Missing data will be assumed to be missing at random.

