**Sample size**

The sample size needed to show a difference in the reduction of the meningitis attack rate will be predicated on multiple factors, some of which can be reliably estimated (risk of developing meningitis among household contacts of cases), and others which cannot be reliably estimated, or which will depend on the study area. The overall size of the epidemic (as measured by cumulative incidence) is not reliably predictable. Average household size and average village size also vary significantly by region of Niger.

Table 2 presents different simulations of the number of clusters necessary given specified attack rates and impacts of the ciprofloxacin intervention under the following hypotheses, using the method detailed by Donner and Klar (1996):

- Risk of type 1 error (alpha) of 5%
- Power of 90%
- Inter-cluster correlation coefficient of 0.025
- Average village population of 300 persons

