**Table 2 : Number of clusters necessary given different attack rates and intervention effectiveness**

| *Reduction in attack rate due to intervention* |  | *Meningitis attack rate in arm receiving standard of care (%)* | | | | | |  |
| --- | --- | --- | --- | --- | --- | --- | --- | --- |
|  |  | 0.5 | 1 | 2 | 3 | 4 | 5 | |
| 50% |  | 355 | 177 | 88 | 58 | 44 | 35 | |
| 70% |  | 157 | 79 | 39 | 26 | 20 | 16 | |
| 90% |  | 81 | 41 | 20 | 14 | 10 | 8 | |

For example, in the situation where the end-of-epidemic attack rate in villages with at least one case is 1%, and the reduction of the attack rate due to ciprofloxacin is 70%, a total of 79 villages would need to be randomized in each arm of the study.

Because of these uncertainties, the overall target sample size necessary will be set after four weeks of accumulated study data. This period is sufficiently long to allow for a description of the demographic co-factors in the study area. Table 2 shows the high variability given these co-factors, but the most likely combinations of scenarios present sample sizes that are logistically feasible.

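### The three-arm primary comparison is to be reported as hazard ratios, but ANOVA and linear regression on village attack rates do not produce them

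*Combined protocol and SAP*

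**What the plan says.** The combined protocol and SAP treats the primary analysis in one paragraph under Data analysis. It opens: "The primary analysis of the difference in attack rate by study arm will be based on the overall meningitis incidence during the epidemic", counted in each arm's villages after they join the study and with allowance for clustering. It then names two sets of methods.

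- Two arms at a time: "Pairwise comparisons will be made between each intervention group using the" Student's t-test.
- All three arms: "ANOVA and multiple linear regression will be used to compare the attack rates between the three study groups, and will be expressed in hazard ratios". Each ratio is to carry a 95% confidence interval.

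The paragraph ends: "The sponsor will be responsible for developing a written analytic plan". That plan is not part of the documents. The Scientific Committee section asks the committee to advise and agree on an analysis plan, but gives no date.

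Elsewhere, Table 2 labels its rows "Reduction in attack rate due to intervention" (50%, 70%, 90%). Its columns are attack rates in the standard-care arm. The surveillance section takes the denominator from a village census.

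**The concern.** A hazard ratio compares event rates over follow-up time. It needs a time origin, a censoring rule, event dates and a model that uses them. None of these is specified for meningitis. The outcome is cumulative incidence over a census population, and the case data listed under Meningitis surveillance and incidence calculations include no onset or presentation date.

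ANOVA gives an F test. Linear regression of village attack rates gives differences in means. The sentence therefore joins a method to an effect measure that the method cannot deliver, and the hazard ratio is the only effect measure with a confidence interval that the plan names for the primary outcome.

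At stake is how the effect is reported. If the sentence stands, someone must replace the effect measure or the model, or a difference may be published under the wrong label. The arms are visibly different and the primary sponsor holds the data and runs the analyses, so that choice is best made before outcomes are examined.

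**Working it through.** **Inputs.** From Sample size: "Risk of type 1 error (alpha) of 5"%, power 90%, "Inter-cluster correlation coefficient of 0.025", average village of 300. From Data analysis: "All P values will be 2-sided". From the example under Table 2: 1% in standard care, 70% reduction (so 0.3%), 79 villages per arm.

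**1. Reproduce the plan's figure.**
- Design effect = 1 + (300 − 1) × 0.025 = 8.475.
- Persons per arm before clustering = (1.960 + 1.282)² × (0.01 × 0.99 + 0.003 × 0.997) / 0.007² = 2,764.
- Villages per arm = 2,764 × 8.475 / 300 = 78.1, against 79 stated.
- The same formula comes within about one village of all 18 cells of Table 2. The table rests on two attack-rate proportions and uses no hazard.

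**2. What the linear comparison returns.**
- Effective persons per arm = 79 × 300 / 8.475 = 2,796.
- SE of the difference = √[(0.0099 + 0.002991) / 2,796] = 0.00215.
- Difference = −0.0070 ± 1.96 × 0.00215, that is −0.70 percentage points (−1.12 to −0.28).

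This is the two-arm comparison. If both ciprofloxacin arms were at 0.3% and the regression pooled residual variance over three arms, the SE would be 0.00195 and the limits −1.08 to −0.32. The scale is the same.

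**3. The ratio for the same scenario.**
- SE of log ratio = √[0.99 / (0.01 × 2,796) + 0.997 / (0.003 × 2,796)] = 0.393.
- Attack-rate ratio = 0.30, with limits 0.30 × exp(±1.96 × 0.393) = 0.14 to 0.65.
- Hazard ratio, assuming proportional hazards and complete follow-up = ln(0.997) / ln(0.99) = 0.299.

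**4. Can the linear output be turned into a ratio by a routine step?**
- Exponentiating the coefficient: exp(−0.0070) = 0.993, which is nowhere near 0.30.
- Taking logs of village attack rates: under a beta-binomial distribution with the plan's correlation, and not counting the triggering case, about 43% of villages at 1% and 78% at 0.3% have no cases. Their log is undefined, and the plan gives no rule for zeros.

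**5. Does follow-up time matter?** Villages join at their first case after the health area opens, and incidence is assessed until the epidemic ends. Observation time therefore differs between villages. An analysis using only the census denominator gives an attack-rate ratio. An incidence rate ratio also needs follow-up time.

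**The case against.** The strongest reply is that little is lost. The paragraph itself opens with a difference in attack rate, and the named tests provide that difference, an interval and a p-value. With rare events the hazard ratio and the attack-rate ratio almost coincide (0.299 and 0.300 above), so the label looks like a slip. A separate analysis plan is required and can put it right.

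Most of this stands, and it rules out several stronger readings that a reader might infer.

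- *That the primary result cannot be computed at all.* It can, as a difference; step 2 does so.
- *That the analyst must choose a model after seeing the data.* The documents call for an agreed analysis plan. Because no date is set for it, late choice is a risk, but it is not forced.
- *That the trial can only want a ratio.* Table 2 speaks of relative reductions, while Data analysis speaks of a difference. The documents support either.
- *That village counts are too small for a linear model, which would give negative attack rates.* At 1% with correlation 0.025, about 27% of villages exceed three cases and the 95th percentile is 13. In the worked example the limits for the 0.3% arm stay above zero: 0.10% to 0.50% with that arm's own variance, and 0.002% to 0.60% with variance pooled over the two arms.

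What the reply does not remove is the sentence itself. Near-equality of two ratios shows what may have been meant, but it does not make a linear model estimate either one. The allowance for clustering concerns the standard error and leaves the effect scale open. A later plan that got this right would have to contradict the protocol.

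**Conclusion.** The concern holds in a limited form. The effect measure named for the three-arm primary comparison does not match the models named to produce it, and nothing else in the documents supplies a model that would. The hypothesis tests, the attack-rate difference and the sample sizes in Table 2 are not affected.

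The figures of −0.70 points (−1.12 to −0.28) and 0.30 (0.14 to 0.65) describe one scenario on two scales. They show that the scales are not interchangeable, and they do not measure bias. They rest on the plan's own assumptions of equal villages of 300 and a correlation of 0.025, and on normal approximations. This should be corrected before outcome data are examined. It is not a reason to hold the trial.

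**What to change.** In Data analysis, delete the reference to hazard ratios. Before outcome data are examined, name one effect measure and a village-level method that yields it, in both the protocol and the analytic plan. Two coherent choices are:

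- **Attack-rate ratio.** Since Table 2 is set out in relative reductions, this is a natural choice. Estimate each pairwise ratio with 95% CI from a village-level overdispersed count model, for example negative binomial, with log census population as offset. Add log follow-up time if an incidence rate ratio is wanted. Keep the village-level t-test, or a permutation test of the allocation, as a check on the p-value.
- **Attack-rate difference.** Keep the linear model and report the difference with its 95% CI.

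State also whether the triggering case counts. Data analysis refers to incidence after inclusion, while the Table 2 example refers to villages with at least one case. One case in a village of 300 is already 0.33%, above the 0.3% assumed under a 70% reduction, so the answer affects either measure.

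The cost is a short text change. Case counts and the census are already planned, so the attack-rate ratio and the difference need no new data. An incidence rate ratio also needs each village's inclusion date and the end date of follow-up.

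### The reported confidence intervals come from three-group ANOVA and regression, which ordinarily pool one variance over arms whose village-level variances differ about 2- to 10-fold on the plan's own figures; arm-specific or robust variances should be specified.

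*Combined protocol and SAP*

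**What the plan says.** The Data analysis section describes two layers of comparison. The first is pairwise: "Pairwise comparisons will be made between each intervention group using the student’s t-test". The second covers all arms together: "ANOVA and multiple linear regression will be used to compare the attack rates between the three study groups". The results of that second layer "will be expressed in hazard ratios with 95% confidence intervals". The t-test sentence mentions neither an effect estimate nor an interval, so as written the reported intervals belong to the ANOVA and regression layer.

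The primary analysis is to be done "taking into account the cluster-randomized nature of the trial", but no method is given. The section does not state the variance estimator, the scale of the outcome (raw or log attack rate), or whether the t-test or the regression decides a pairwise question. It adds "The sponsor will be responsible for developing a written analytic plan"; that plan is not part of these documents. The significance rule is "All P values will be 2-sided with *p* < 0.05 considered statistically significant".

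The Sample size section assumes "Inter-cluster correlation coefficient of 0.025", one value for all arms, with an average of 300 people per village. Table 2 covers reductions of 50%, 70% and 90%. In its worked example (1% attack rate), "the reduction of the attack rate due to ciprofloxacin is 70%, a total of 79 villages would need to be randomized" in each arm.

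**The concern.** The variance of a village's attack rate depends on the rate itself. If prophylaxis lowers the rate, it also lowers the spread between villages. A model with one residual variance averages the small variance of an effective arm with the larger variances of the others. A contrast between two unaffected arms then looks more precise than it is, and a contrast involving the effective arm looks less precise than it is.

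The outcome most exposed is one that a three-arm trial has to be able to distinguish: village-wide prophylaxis works and household prophylaxis does not. The study rationale itself raises the possibility that the village-wide strategy is the more effective. In that case the success of one arm would make a false claim for the other more likely. A report could also show a regression interval that excludes no effect beside a non-significant t-test for the same contrast, with no rule for choosing between them.

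**Working it through.** **Inputs.** From the Sample size section: intracluster correlation ρ = 0.025, village size m = 300, two-sided alpha 5%, power 90%. From Table 2: attack rates 0.5–5%, reductions 50%, 70% and 90%, and the village numbers.

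**Reproducing Table 2.** The design effect is 1 + 299 × 0.025 = 8.475. The formula with arm-specific variances is

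k = (1.960 + 1.282)² × [p₁(1−p₁) + p₂(1−p₂)] / (p₁−p₂)² × 8.475/300.

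For 1% against 0.3% it gives 78.09, rounded up to the stated 79. Rounded up, it matches 17 of the 18 cells. The exception is 1% with a 90% reduction: 39.94, hence 40, against 41 stated. The version with pooled variance under the null and arm-specific variance under the alternative gives 40.03 there, hence 41, and matches all 18 cells.

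**Village-level variance.** V(p) = p(1−p)[ρ + (1−ρ)/m] = p(1−p) × 0.02825.

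| Attack rate | V(p) | SD |
|---|---|---|
| 1% (standard) | 2.797 × 10⁻⁴ | 1.67% |
| 0.3% (70% reduction) | 8.45 × 10⁻⁵ | 0.92% |
| 0.1% (90% reduction) | 2.82 × 10⁻⁵ | 0.53% |

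Over the attack rates in Table 2, the ratio of standard-care variance to effective-arm variance is 1.95–1.99 at a 50% reduction, 3.2–3.3 at 70% and 9.6–9.95 at 90%.

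**Effect of pooling on household versus standard.** Let the household arm have no effect (variance V) and the village-wide arm be effective (variance V_c). With equal arms, the pooled variance is (2V + V_c)/3. In the worked example it is (2 × 2.797 + 0.845)/3 × 10⁻⁴ = 2.146 × 10⁻⁴. The model standard error is therefore √(2.146/2.797) = 0.876 of the true one. The false-positive rate is 2[1 − Φ(1.96 × 0.876)] = 8.6%, and the nominal 95% interval covers about 91.4%. At a 1% attack rate with 50% and 90% reductions, the ratios are 0.913 and 0.837, giving 7.3% and 10.1%.

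**Effect on village-wide versus standard.** The pooled standard error is too large by √[2 × 2.146/(2.797 + 0.845)] = 1.086, so intervals are about 8.6% too wide in the worked example.

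**Simulation.** Beta-binomial villages of 300, village numbers from Table 2, 20,000 to 40,000 trials per scenario, several independent runs:

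| Standard rate, village-wide reduction, villages per arm | False positives, household vs standard: pooled regression | Same: two-sample t |
|---|---|---|
| 1%, 50%, 177 | 7.2–7.3% | 4.8–5.0% |
| 1%, 70%, 79 | 8.4–8.7% | 4.9–5.0% |
| 1%, 90%, 41 | 10.2–10.4% | 4.6–4.9% |
| 2%, 90%, 20 | 9.8–10.2% | 4.5–4.6% |

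HC3 standard errors gave 4.9%, 4.8%, 4.4% and 4.1% in the same four settings. Power for village-wide versus standard at 79 villages was 88.6–89.0% with pooled regression and 92.3–92.6% with arm-specific variance. At 20 villages (2%, 90%) it was about 89% against about 95%.

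At 79 villages, the regression is significant and the t-test is not in about 3.6–3.7% of trials for household versus standard.

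**When no arm works.** The three-group F-test was significant in 4.6–5.1% of trials.

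**The case against.** The strongest reply is that household versus standard is a pairwise comparison, and for those the plan names Student's t-test. That test uses only the two arms concerned, whose variances are equal when household prophylaxis has no effect, and it holds about 5%. This stands. A reader might infer that the plan's household-versus-standard test simply runs at 7–10%; the documents do not support that. What remains is that the intervals are attached to the other layer and no rule says which layer governs.

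Second, pooling on raw rates is the ordinary form of the named methods but is not stated. The plan asks for hazard ratios, which linear regression on attack rates does not give, so the scale is open. On an assumed log(cases + 0.5) scale, simulated rates ran from about 3.8% to 9.6% across scenarios, so the size, and in some settings the direction, depends on an unspecified choice. This also stands. It limits the figures but is itself a reason to specify the model.

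Third, a reader might infer that Table 2 was built on arm-specific variances, so that the sizing and the analysis contradict each other. The table does not show this: the formula that fits all 18 cells pools the variance under the null.

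Fourth, the detail is left to a written analytic plan on which the Scientific Committee is to advise. Nothing in the protocol prevents that plan from using Welch or robust variances, but nothing in these documents yet provides for them.

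**Conclusion.** The point holds as a conditional one. The household-versus-standard interval from the regression is too narrow, with false-positive rates of about 7%, 8.5% and 10% at village-wide reductions of 50%, 70% and 90%, if all of the following apply:

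- household prophylaxis has no effect and village-wide prophylaxis is effective to that degree;
- the intracluster correlation is 0.025 in every arm, with villages of 300 and equal numbers of villages per arm;
- raw attack rates are modelled with the default single residual variance.

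Under the same conditions, intervals involving the village-wide arm are too wide. In the worked example this takes power slightly below the 90% target, whereas the t-test stays above it.

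It would go too far to say that the main results are wrong in general. The named pairwise test is sound for household versus standard, and the omnibus test is at about 5% if neither intervention works. The defect is that intervals are drawn from a method whose usual variance assumption conflicts with the plan's own inputs, and that two analyses of one contrast can disagree with no order of precedence. This is a should-fix, not a must-fix.

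**What to change.** In the Data analysis section, or in the analytic plan before any outcome data by arm are examined, specify variances that may differ between arms. Either Welch ANOVA with Welch pairwise contrasts, or the same linear regression with HC3 standard errors, would do. State that each contrast's estimate, 95% confidence interval and p-value all come from that one analysis, so that no second test of the same contrast competes with it. State the outcome scale as well, since the intended effect measure does not follow from linear regression on attack rates.

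The cost is a sentence or two of text and a software option, with no extra villages or data. In the worked example the household-versus-standard interval becomes about 14% wider (1/0.876 = 1.14), which is its correct width; the village-wide contrasts gain precision. HC3 is slightly conservative when villages are few (4.1% simulated at 20 per arm).

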**STUDY OBJECTIVES**

Primary objective

Compare the incidence of meningitis among villages receiving standard care, household ciprofloxacin prophylaxis and village-wide prophylaxis.

Secondary objectives:

- Compare the incidence of meningitis by sex in the three different intervention areas.
- Compare the incidence of meningitis by age in the three different intervention areas.
- Estimate the individual efficacy of oral ciprofloxacin for the prevention of meningitis.

Substudy objective:

Compare the prevalence of enterobacteriaceae resistant to ciprofloxacin before and after distributions of ciprofloxacin in communities receiving distributions versus in communities not receiving distributions.

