Once a participant has been included in the resistance sub-study, the study team will make every reasonable effort to ensure his or her participation for the entire study period. It is projected that attrition rate will be 25% and that up to 20% of samples will be inappropriately conserved and therefore be not able to be analyzed. The sponsor will be responsible for developing study SOPs to achieve this level of follow-up. Soap will be provided with each stool sample container so as to give sensitization messages about handwashing and to ensure that participants are able to wash their hands after sample collection (see Reimbursement below).

*Sample size considerations*

Assuming a baseline prevalence of enterobacteriaceae resistant to ciprofloxacin in the community of 20%, over three repeated visits, a sample size of 131 persons in each of the two arms would have 90% power to detect a change in the prevalence to 30%. Assuming an attrition rate of 25% and 20% of improperly collected samples, a sample size of 200 persons per arm would allow for the calculation of the primary resistance objective with sufficient power.

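### The resistance sub-study is powered to compare prevalence between arms, but its analysis names only acquisition rates in a per-protocol, three-stool set and no between-arm contrast

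*Combined protocol and SAP*

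**What the plan says.** The sub-study objective (Study objectives) is a comparison of resistance prevalence "before and after distributions of ciprofloxacin in communities receiving distributions versus in communities not receiving distributions". The sample size (Resistance sub-study) is for the same quantity: "Assuming a baseline prevalence of enterobacteriaceae resistant to ciprofloxacin in the community of 20%, over three repeated visits", 131 people per arm "would have 90% power to detect a change in the prevalence to 30"%. The protocol raises this to 200 per arm for 25% attrition and 20% improperly collected samples. Recruitment is 20 people in each of 10 villages per arm, with stools at Days 0, 7 and 28.

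The Data analysis section says that the sub-study analysis "will be done on the basis of the per-protocol population for whom all three stool samples are available". Acquisition rates at Days 7 and 28 "will be calculated with corresponding 95% confidence intervals using the binomial distribution". The next sentence says that the nested, cluster-randomised selection will be allowed for, without naming a method. The section closes with "Missing data will be assumed to be missing at random". Per-protocol and acquisition are not defined, and no effect measure, model or between-arm test is given for the sub-study. A written analytic plan is left to the sponsor and is not among the documents.

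**The concern.** The quantity the sub-study is powered for is not the quantity the analysis section describes. The objective needs the change in prevalence in distribution villages set against the change in standard-care villages. Acquisition rates with intervals do not by themselves make that comparison. As usually defined, they also leave out people already positive at Day 0, about 20% on the protocol's own assumption.

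Membership of the analysis set is settled after randomisation. If per-protocol means having taken ciprofloxacin, it excludes people in the community arm only, although non-takers belong to the communities named in the objective. Day 0 stools are also accepted only until the drug is given in the village, and no matching cut-off is stated for standard care. Missing Day 0 stools could therefore differ by arm.

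The stakes are real. The Ethical considerations section says that, even if the primary outcome is positive, routine use would not be recommended without a description of the effect on resistance. This sub-study supplies that description.

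**Working it through.** **Inputs.** From the Resistance sub-study section: prevalence 20% against 30%, 90% power, three visits, 131 evaluable and 200 enrolled per arm, 25% attrition, up to 20% unusable samples, 10 villages of 20 people per arm. From Data analysis: "All P values will be 2-sided with" a threshold of "0.05 considered statistically significant". The documents give no intracluster correlation (ICC) for resistance; 0.025 to 0.10 is assumed here. (The protocol's 0.025 is for meningitis.)

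**1. Reproducing 131.** The protocol does not state its formula. The usual two-proportion formula with pooled null variance gives

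n = [1.960·√(2·0.25·0.75) + 1.282·√(0.2·0.8 + 0.3·0.7)]² / 0.10² = 392 per arm.

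Dividing by three visits gives 392/3 = 130.7, so 131. This is n(1 + 2ρ)/3 with within-person correlation ρ = 0 and no village design effect.

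**2. From 131 to 200.** Dividing by the retained fractions gives 131/(0.75 × 0.80) = 218.3, so 219. Multiplying up gives 131 × 1.25 × 1.20 = 196.5, close to 200.

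**3. People with all three stools, from 200 per arm.**
- 20% applied once per person: 200 × 0.75 × 0.80 = 120 (60%).
- 20% applied independently to each stool: 200 × 0.75 × 0.80³ = 76.8, about 77 (38%).

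Both are below 131. Ending with 131 would need 219 or 131/0.384 = 341.1, so 342, enrolled per arm.

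**4. Power on the basis of step 1.** With 3 × 77 = 231 and 3 × 120 = 360 observations per arm treated as independent, power is about 70% and 87%.

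**5. What the three-stool rule itself discards.** Usable stools per arm:
- all attrition before Day 7: 200 × (1 + 0.75 + 0.75) × 0.80 = 400;
- all attrition after Day 7: 200 × (1 + 1 + 0.75) × 0.80 = 440.

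Stools retained by the rule are 3 × 120 = 360 or 3 × 76.8 = 230.4.

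| Unusable samples | Discarded of 400 | Discarded of 440 |
| --- | --- | --- |
| fall in the same people | 10% | 18% |
| independent by stool | 42% | 48% |

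On the independent reading, using every usable pair with Day 0 would keep 200 × 0.75 × 0.80² = 96 people per arm at Day 28, and 96 to 128 at Day 7, against 77.

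**6. Clustering.** The three-stool set has 77/10 = 7.7 to 120/10 = 12 people per village. The design effect is 1 + (m − 1) × ICC:
- m = 7.7, ICC 0.025: 1.17; binomial SE too small by 1 − 1/√1.17 = 7%.
- m = 12, ICC 0.10: 2.10; binomial SE too small by 1 − 1/√2.10 = 31%.

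Restricting to people negative at Day 0 would lower m, and the design effect, further.

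**The case against.** The strongest reply is that the analysis section is a sketch. It defers to a written analytic plan, on which the Scientific Committee is to advise and agree, and that plan could add a between-arm test. This stands to the extent that the fault is an unspecified test, not a decision against testing. It does not remove the mismatch, because the analysis set and the summary measure are stated now and neither serves the objective.

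Four stronger readings are tempting, and the documents do not support them:
- **The rule throws away about half the data.** Much of the shortfall is attrition, meaning stools never collected. The 20% is stated as an upper limit, and the overlap of losses is unknown. The supportable range is 10% to 48% of usable stools.
- **Clustering is ignored.** The protocol says nesting will be allowed for. The difficulty is that the only interval it names does not do this, so the two sentences need reconciling.
- **Non-takers are removed.** The protocol records whether each participant received the drug but never says this defines the per-protocol set. The phrase may mean only that samples are available.
- **Complete-case analysis contradicts the missing-at-random statement.** It does not. That sentence is general to the section, and the three-stool rule merely fails to use it.

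**Conclusion.** The concern holds in this form: the objective and sample size call for a between-arm comparison of prevalence change, while the stated analysis gives acquisition rates in a set selected after randomisation and names no contrast between arms.

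At the protocol's planning losses the set is 77 to 120 per arm against 131 required. The range depends on whether the 20% applies per stool, independently, or per person. The 70% to 87% power rests on a reconstructed formula with no within-person correlation and no clustering, so it measures the shortfall on the plan's own terms and does not forecast actual power. With ρ = 0.5 the same formula needs 392 × 2/3 = 261.3, so 262 per arm. Changing the analysis recovers usable stools and tests the right quantity; it does not by itself secure 90% power.

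The 7% to 31% understatement of the standard error applies only if a plain binomial interval is used, and depends on the assumed ICC. The direction of any selection bias cannot be judged from the documents.

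**What to change.** In the Data analysis section and the written analytic plan:
- Make the primary sub-study analysis a comparison of resistance prevalence by village allocation, using all usable stools from all enrolled participants.
- Fit arm, visit and arm-by-visit terms, allowing for village and participant clustering, with a small-sample correction suited to 10 villages per arm. A logistic mixed model or GEE would serve if it carries that correction.
- Name the arm-by-visit contrasts at Days 7 and 28 as the test of the objective.
- Define per-protocol and acquisition. Keep acquisition rates in the three-stool per-protocol set as a secondary analysis, with cluster-adjusted intervals in place of plain binomial ones.

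The same participants, visits and samples are used. The cost is analysis work only.
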